#### Conditions and Procedures for Participant Withdrawal

There are two routes for participant withdrawal.

Withdrawal determined by the investigator: This may occur when a participant already enrolled in the study becomes unsuitable for continued participation due to the development of complications, comorbidities, or special physiological changes. Other conditions include poor compliance, defined as taking less than 80% or more than 120% of the prescribed medication, and the use of prohibited medications as per protocol.

Participant-initiated withdrawal: According to the informed consent form, participants have the right to withdraw at any time. If a participant stops taking the medication or attending visits without formally withdrawing, they are still considered “withdrawn” (or “lost to follow-up”). Reasons for withdrawal should be documented where possible and may include feeling the treatment is ineffective, the development of intolerable adverse reactions, personal circumstances, financial reasons, or unexplained loss to follow-up.

Regardless of the reason, case report forms for withdrawn participants should be retained. The last recorded test results will be used as final data, and both efficacy and adverse events will be analyzed in the full dataset.

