### Randomization

Random numbers will be generated using SAS statistical software (version 9.4), and participants will be assigned to the intervention and control groups in a 1:1 ratio. After screening and informed consent, patients will be randomly assigned to one of the two groups based on their order of enrolment. The drug number for each participant will remain unchanged throughout the study. In the case of a clinical emergency, the participant’s random code and group assignment may be unblinded.

Due to the nature of the intervention, participant and clinician blinding is not feasible. However, outcome assessors will be blinded to group assignments to minimize detection bias, especially for subjective measures such as TCM symptom scores.

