### Statistical Analysis

#### Definition and Selection of Statistical Analysis Datasets

Participants will be categorized into the following analysis sets:

Full analysis set: This includes all randomized participants who have at least 1 postbaseline efficacy evaluation. This is the main dataset for efficacy analysis. Missing values for primary efficacy outcomes will be imputed using the last observation carried forward method. Missing values for secondary efficacy and safety outcomes will not be imputed. For secondary efficacy endpoints and safety data, descriptive analysis and complete-case analysis will be conducted based on actual observed values. Although last observation carried forward is commonly used in clinical trials, we acknowledge its limitations in progressive conditions such as stroke recovery. We will perform sensitivity analyses using multiple imputation methods to evaluate the robustness of our results.Per protocol set: This includes all participants in the full analysis set who meet inclusion criteria, do not meet exclusion criteria, complete the treatment, and do not have major protocol deviations. This is the secondary dataset for efficacy evaluation.Safety set: This includes all randomized participants who received at least 1 dose of Qizhi Jieyu pill and had at least 1 postbaseline safety evaluation.

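### Two conflicting missing-data rules cover withdrawn participants' TCM and Rankin scores, and the complete-case rule can bias the comparison if dropout differs between arms

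*Protocol article*

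**What the plan says.** Two sections of the Protocol article set a rule.

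- **Definition and Selection of Statistical Analysis Datasets.** For the primary outcome: "Missing values for primary efficacy outcomes will be imputed using the last observation carried forward method". For the rest: "Missing values for secondary efficacy and safety outcomes will not be imputed", followed by "For secondary efficacy endpoints and safety data, descriptive analysis and complete-case analysis will be conducted based on actual observed values". After conceding the limits of carrying values forward in stroke recovery, the section adds: "We will perform sensitivity analyses using multiple imputation methods to evaluate the robustness of our results". It does not name the outcomes that this covers.
- **Conditions and Procedures for Participant Withdrawal.** Whatever the reason for leaving, "The last recorded test results will be used as final data, and both efficacy and adverse events will be analyzed in the full dataset". The sentence does not single out the primary outcome. The reasons for participant-initiated withdrawal "may include feeling the treatment is ineffective, the development of intolerable adverse reactions", among others.

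Four other places matter. Randomization states that "participant and clinician blinding is not feasible", although outcome assessors are blinded. Table 1 schedules the TCM and Rankin scores at baseline and at weeks 12, 24, 36 and 48. Sample Size Calculation allows for 20% dropout with 63 per group. Secondary Outcomes divides recurrent cases by everyone in the study, which is a separate rule for recurrence.

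**The concern.** A participant who leaves after week 24 has a week-48 TCM or Rankin value under the withdrawal section (the week-24 score carried forward). Under the analysis-sets section that value is missing. This is not detail deferred to a separate analysis plan, because both rules are written here and they differ. The analysis plan is to be finalised only before database lock, so the choice could be made late in a trial whose clinicians know the allocation.

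The complete-case rule is also a weak choice on the protocol's own facts. The protocol foresees people leaving because of "feeling the treatment is ineffective", so those still observed may be better responders than their arm as a whole. An analysis of a later visit restricted to people observed there makes no use of the scores that dropouts gave at earlier visits, although those scores carry information about the missing value. The TCM and Rankin comparisons are at stake. The primary outcome has its own stated rule and a planned sensitivity analysis.

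**Working it through.** **1. The protocol's own figures.** The 63 per group reproduces as 52 × 1.2 = 62.4, rounded up. The planned dropout per group is 63 × 0.20 = 12.6, about 13, leaving 63 × 0.80 = 50.4.

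**2. The two rules side by side, for a participant who withdraws between visits.**

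| Outcome at a later visit | Withdrawal section | Analysis-sets section |
|---|---|---|
| NIHSS | last value carried forward | last value carried forward |
| TCM score | last value carried forward | missing, excluded |
| Rankin score | last value carried forward | missing, excluded |

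The rules agree for the primary outcome and disagree for the two secondary scores. About 13 of 63 per arm is an upper limit. It applies to a comparison at a late visit, with all dropouts having at least one score after baseline.

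**3. Size of the complete-case bias.** The documents give no figure for how strongly dropout depends on response or how it splits by arm, so both are assumptions. Take an outcome with SD 1, coded so that higher is better, and no true difference between arms. Let dropout depend on a latent variable correlated ρ with the outcome, the worst fraction d leaving. The mean among those who stay is shifted upward by

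shift(d) = ρ × φ(z_d) / (1 − d),

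where z_d is the standard normal quantile at d and φ the normal density. The between-arm bias (study minus control) is shift(d_study) − shift(d_control).

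The factor φ(z_d)/(1 − d) is:
- d = 0.10: 0.1755/0.90 = 0.195
- d = 0.15: 0.2332/0.85 = 0.274
- d = 0.25: 0.3178/0.75 = 0.424
- d = 0.30: 0.3477/0.70 = 0.497

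With overall dropout held at 20%:

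| Dropout control / study | ρ = 0.3 | ρ = 0.5 | ρ = 0.8 |
|---|---|---|---|
| 20% / 20% | 0 | 0 | 0 |
| 25% / 15% | −0.04 | −0.08 (simulated) | −0.12 |
| 30% / 10% | −0.09 | −0.15 | −0.24 |
| 15% / 25% | +0.04 | +0.08 (simulated) | +0.12 |

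A simulation with 4,000,000 participants per arm agrees. For 25%/15% it gave −0.044, −0.076 and −0.121, against −0.045, −0.075 and −0.120 from the formula. With ρ = 0 the bias is about 0 for every split. The sign follows the arm that loses more: heavier loss from control works against the pill, heavier loss from the study arm works in its favour.

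**4. Scale.** With 50 analysed per arm, the standard error of a standardised difference is √(2/50) = 0.20 SD. A bias of 0.04 to 0.24 SD is therefore 0.2 to 1.2 standard errors.

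**5. Whether earlier scores help.** In a second simulation, 20% dropout was driven by the week-12 score, with an assumed correlation of 0.7 between weeks 12 and 48. At assumed odds ratios of 1.65 and 2.72 per SD, the completer mean in one arm shifted by 0.069 and 0.123 SD. Using the week-12 score in a regression reduced this to about 0.001 SD. That gain depends on dropout being explained by scores already observed.

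**6. Recurrence.** Dividing by everyone counts an unobserved participant as recurrence-free. With an assumed true rate of 10% and 20% unobserved at the same rate, this gives 10% × 0.8 = 8%, against 10% among those observed.

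**The case against.** The best reply is that the withdrawal section is a general statement about keeping data, while the analysis-sets section is the specific statistical rule and should govern. That is a reasonable way to resolve the conflict, but the text does not say so. The withdrawal sentence speaks of efficacy in general and of final data, which reads as carry-forward.

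A second reply also has force. Secondary Outcomes does not fix week 48 for the TCM or Rankin comparison. It speaks of before and after medication, or before and after treatment, and the intervention lasts 12 weeks. If the comparison is at week 12, a participant who leaves later is a complete case, and one who leaves before any efficacy assessment is outside the full analysis set. Little of the problem would then remain.

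Four stronger readings are tempting and are not supported:

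- *Multiple imputation is confined to the primary outcome.* Its sentence follows the carry-forward caveat, but refers only to results in general. Coverage of secondary outcomes is unstated, not excluded.
- *Poor responders in the control arm will leave, so the bias has a known sign.* The listed reasons apply to any participant. Adverse reactions and the medication-compliance limits may fall more on the study arm. If control did lose more poor responders, the bias would work against the pill.
- *The 0.07 to 0.12 SD shift is the bias in the trial result.* It is the shift in one arm's mean on assumed inputs. With the same amount and mechanism of dropout in both arms, the difference between arms is unbiased.
- *The fall from 63 to about 50 analysed per arm is a new loss.* It is the dropout allowance already in the sample size.

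**Conclusion.** The contradiction stands in the current text and affects two of the three secondary outcomes, for up to about 13 of 63 participants per arm at the planned dropout and a late-visit comparison. Recurrence has its own denominator and is not simply complete-case.

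The bias is conditional. It requires withdrawal to depend on response and to differ between arms in amount or mechanism. An open-label add-on trial, in which only one arm takes the pill, makes that plausible but not certain. In the cases worked here it ranges from about 0 with equal dropout to 0.24 SD at 30%/10%, on assumed correlations of 0.3 to 0.8. Its direction cannot be settled from the documents. The change is worth making because it is cheap and uses data already scheduled. The primary analysis is not affected.

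**What to change.** 1. In Conditions and Procedures for Participant Withdrawal, remove carry-forward for secondary outcomes only. Keep the commitment to analyse withdrawn participants' efficacy and adverse events in the full dataset; deleting the whole sentence would lose it. Refer to the statistical section for the handling of missing values.
2. In Definition and Selection of Statistical Analysis Datasets, state the same single rule and name the visit at which the TCM and Rankin scores are compared.
3. Make the main secondary analysis one that uses all scheduled visits: a repeated-measures mixed model or multiple imputation for the TCM score, and an ordinal model with the same use of earlier visits for the Rankin score, with death kept as level 6. Keep complete-case as a sensitivity analysis.
4. Say which outcomes the multiple-imputation sentence covers.
5. State that recurrence follows the denominator given under Secondary Outcomes.

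The cost is wording and modest extra programming, since multiple imputation is already planned. The analysis would rest on a missing-at-random assumption. It corrects for dropout explained by observed scores, but not for dropout driven by unrecorded change after the last visit.

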### Sample Size Calculation

The clinical sample size was calculated using a 2-group mean difference test (shown below), where n is the required sample size per group, σ is the pooled SD of the 2 groups, α is the type 1 error, β is the type 2 error, and δ is the expected mean difference between the study and control groups.

Since there are currently no direct data available to calculate the clinical sample size, we mainly referred to 2 clinical studies [15,16]. In these studies, the NIHSS score change value in the control group (conventional treatment) was approximately 4.9. The pooled SD (σ) was estimated based on prior studies that reported SDs ranging from 1.5 to 2.5. We conservatively used σ=2.0 in our calculation to ensure adequate power. It is hypothesized that the change in the study group (conventional treatment plus Qizhi Jieyu pills) would be approximately 6, with a mean difference of 2 between the 2 groups. Assuming a 1:1 sample ratio between the control and study groups with α=0.05 and β=0.2, the required sample size per group is 52. Considering an overall dropout rate of 20%, each group needs 63 participants, for a total of 126 participants. A third-party group composed of experts in TCM, endocrinology, and statistics will be organized at the midterm of the study to reassess the sample size based on the observed effect size of the primary efficacy indicators and associated errors. Figure 1 shows the study flowchart.

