### Intervention

Referring to the guidelines for clinical management of cerebrovascular diseases in China (second edition) [20], both groups will receive conventional rehabilitation training guidance, including assessment and rehabilitation of cognitive function, speech ability, swallowing function, limb motor and sensory function, balance, psychological state, and daily living abilities. They will also receive standard treatments such as antiplatelet therapy, lipid-lowering and blood pressure control, plaque stabilization, and electrolyte balance maintenance.

On the basis of conventional treatment, the study group will take Qizhi Jieyu pills, 9 g per dose, twice daily after meals. The control group will receive conventional treatment only. The intervention period is 12 weeks, with a total follow-up period of 48 weeks.

All TCM drugs with the same therapeutic effect as the investigational drug (including those with similar indications or efficacy stated in the instructions) are prohibited during the study. All concomitant medications and treatments (ie, for other diseases) must be recorded in the concomitant medication log.

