#### Statistical Analysis Plan

A statistical analysis plan was formulated prior to the start of the study. It will be finalized after discussion among the statisticians, principal investigators, and sponsor before database lock. This plan describes only the standard statistical requirements.

Statistical analysis will be conducted using SAS version 9.4. All hypothesis tests will be 2-sided, with a significance level of α=.05. *P* values less than or equal to .05 will be considered statistically significant.

For continuous variables, mean, SD, minimum, maximum, and median values will be used for descriptive statistics. Independent samples *t* tests (for normally distributed data) or Wilcoxon rank-sum tests (for non-normally distributed data) will be used for hypothesis testing. Normality of continuous variables will be assessed using the Shapiro-Wilk test before choosing appropriate parametric or nonparametric tests.

For categorical variables, frequency and percentages will be used for description. Chi-square tests or Fisher exact tests will be used for hypothesis testing. Ordinal variables will be analyzed using the Wilcoxon rank-sum test.

Logistic regression will be used to control for confounding factors affecting the outcome measures. We will also analyze the association between syndrome evolution patterns and therapeutic efficacy. In parallel, multivariate linear regression will be used to explore the relationship between outcomes and potential confounders, such as baseline NIHSS score, study center, age, and sex. For adverse events potentially associated with animal-derived components—including itching, rash, allergic reactions, and gastrointestinal discomfort—we will conduct attribution analysis and report their incidence separately.

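### The safety set as defined admits no control participant, so no between-group safety comparison can be made within it

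*Protocol article*

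**What the plan says.** The protocol article, under Definition and Selection of Statistical Analysis Datasets, names three sets. The full analysis set and the per protocol set are described as the main and secondary datasets for efficacy. The third is the safety set: "This includes all randomized participants who received at least 1 dose of Qizhi Jieyu pill and had at least 1 postbaseline safety evaluation". No other safety population is defined.

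Under Intervention, the pill is given to one arm only: "On the basis of conventional treatment, the study group will take Qizhi Jieyu pills". For the other arm: "The control group will receive conventional treatment only". There is no placebo.

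Under Conditions and Procedures for Participant Withdrawal, a paragraph on participants who withdraw ends by saying that "both efficacy and adverse events will be analyzed in the full dataset". The article does not say which of the three sets, if any, this refers to.

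The Introduction gives efficacy and safety together as what the randomized trial is to evaluate. Study Procedures, Table 1 and Safety Outcomes schedule safety assessments through week 48 for all enrolled participants, without distinction by arm.

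**The concern.** Membership of the safety set depends on taking a product that only one arm receives. Applied literally, the rule removes the whole control arm from the population that carries the safety label.

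What is at stake is the interpretation of the safety results. Both arms have had a recent infarction, and both receive antiplatelet, lipid-lowering and blood-pressure treatment, so adverse events are to be expected in both. An event rate in the pill arm alone cannot separate an effect of the pill from the disease or the background treatment. The Statistical Analysis Plan section also promises an attribution analysis of itching, rash, allergic reactions and gastrointestinal discomfort. These are non-specific events, for which the concurrent control rate is the natural reference.

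**Working it through.** **Inputs, all from the protocol article**
- Planned size (Sample Size Calculation): "each group needs 63 participants, for a total of 126 participants".
- Allocation (Randomization): "participants will be assigned to the intervention and control groups in a 1:1 ratio".
- Treatment by arm (Intervention): pill plus conventional treatment, against conventional treatment without placebo.
- Entry to the safety set: at least one dose of the pill **and** at least one safety evaluation after baseline.

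**1. The plan's own sample size.** No figure is stated for the safety set, so the denominators come from the sample size section, which says: "with α=0.05 and β=0.2, the required sample size per group is 52". For two means, n per group = 2σ²(z₁₋α/₂ + z₁₋β)²/δ². The test is two-sided (Statistical Analysis Plan: "All hypothesis tests will be 2-sided, with a significance level of α=.05"), with σ = 2.0 and δ = 6 − 4.9 = 1.1:

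n = 2 × 4 × (1.960 + 0.842)² / 1.21 ≈ 51.9, rounded up to 52.

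This matches. The 20% dropout allowance gives 52 × 1.2 = 62.4, rounded up to 63 per group, and 2 × 63 = 126, which also matches. The difference of 2 stated in the text would give 16 per group instead. That is a separate matter, and nothing below depends on it.

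**2. The safety set definition applied to each arm.**

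| Arm | Randomized | Can meet the dose condition | Most that can enter the set |
|---|---|---|---|
| Qizhi Jieyu pill plus conventional treatment | 63 | up to 63 | 63 |
| Conventional treatment only | 63 | 0 | 0 |
| Total | 126 | up to 63 | 63 |

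Share of randomized participants: 63/126 = 50% at most. Share of controls: 0/63 = 0%.

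**3. Consequence within the set.** The control denominator is zero. A risk difference, a risk ratio, or a chi-square or Fisher test needs a non-empty second group, so none can be computed in this set for any safety outcome.

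**4. The two sections side by side.** The analysis-set section makes a dose of the pill a condition for the safety population. The withdrawal section sends the adverse events of withdrawn participants to a full dataset and sets no such condition. If that term covers both arms, a control who withdraws has adverse events analyzed there but is outside the safety set. If it means something narrower, the article does not say what. The two sections need reconciling on either reading.

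**5. The set after correction.** With controls admitted and participants analyzed by treatment received, the set could hold up to 63 + 63 = 126, that is, up to 63 against 63.

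**The case against.** The literal reading of the definition is hard to dispute. The best counter-argument concerns how far the consequence reaches.

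A reader might infer that the trial can make no comparative safety analysis at all, or that it discards its control safety data. The documents do not support that. The control data are collected. The article never says in terms that safety analyses are confined to the safety set; only the name implies it. The full analysis set paragraph, which covers both arms, mentions safety data when it says observed values will be used without imputation. The withdrawal section places adverse events in a full dataset. The planned tests for categorical variables carry no exception for safety. Recurrent infarction and the Rankin Scale, which includes death, are assessed in both arms as secondary outcomes. This objection stands, and it limits the finding to the set as defined. It does not repair the definition: the sentence under the full analysis set concerns missing values, the withdrawal sentence uses an undefined term, and neither creates a two-arm safety population.

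A reader might also infer that the second condition drops treated participants who stop before the first scheduled visit at week 12. That assumes a safety evaluation means a scheduled visit. Safety Outcomes has adverse events monitored from study entry and recorded throughout, so an early report could itself qualify. The article does not settle the meaning. Requiring some safety evaluation after baseline is also a common convention. The wording therefore deserves a clarification, but it is not a demonstrated loss of participants.

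Finally, this may be a drafting slip, and the analysis plan is still to be finalized before database lock. That bears on how easily it can be corrected. It does not change what the published rule says.

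**Conclusion.** The safety set is wrong as written. It can contain at most 63 of 126 randomized participants (50%) and 0 of 63 controls, so no between-group safety comparison can be made within it. This is a stated rule that gives the wrong population when followed, and not a detail left to a fuller document. It is at odds with the aim of evaluating safety in a randomized comparison and does not sit consistently with the withdrawal section.

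The conclusion rests on two assumptions: that recruitment reaches the planned 63 per arm, and that controls are treated as planned and take no Qizhi Jieyu pill. A control who took the pill off-protocol would meet the dose condition, but that would not supply a control group. The conclusion does not depend on the effect size or dropout rate in the sample size calculation. It concerns the defined set only. The primary efficacy analysis and the data collection are unaffected.

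**What to change.** 1. Redefine the safety set to include randomized participants of both arms, analyzed by treatment actually received. The pill group is everyone who took at least one dose of Qizhi Jieyu pill; the control group is everyone who received conventional treatment only.
2. State that any reported adverse event counts as a post-baseline safety evaluation, so that the second condition cannot be read as requiring attendance at a scheduled visit.
3. Reconcile the withdrawal section with the analysis-set section: either name the defined set in which the adverse events of withdrawn participants are analyzed, or define the full dataset.

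The cost is about one sentence for the definition, plus the matching edits in items 2 and 3. No new data, visits or participants are needed. The article says the analysis plan will be finalized before database lock and that protocol amendments will be recorded in the trial registry, so the change can be made and documented before the data are analyzed. Because treatment is open to participants and clinicians, it is better made now than after safety results by arm are known.
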